### Secondary outcome variables

#### Periodontal probing depth (PPD)

For the investigation of gingival and periodontal status, the PPD will be measured longitudinally from baseline till six months after insertion of the fixed appliance (T0, T1, T2, T3, T4). The measurement of the PPD is performed according to standardized protocols [62, 63]: insertion of a WHO periodontal probe (probe tip with a diameter of 0.50 mm) into the gingival sulcus with a force of 0.2–0.3 N [64, 65]; probing depth is read out at landmarks on the WHO periodontal probe [62, 63]. The scores will be measured full-mouth at four sites per tooth, added and divided by four to obtain the ‘PPD for the tooth’-Index. We will use the ‘PPD for the tooth’, but only for ‘defined teeth’ (explained above for GI). The ‘PPD for the patient’ is then the mean of the PPDs of the ‘defined teeth’.

### Modified Plaque Index (MPI) by Attin et al*.* [66]

For the evaluation of oral hygiene, the MPI will be measured longitudinally from baseline till 6 months after insertion of the fixed appliance (T0, T1, T2, T3, T4). The measurement of MPI is described by Attin et al*.* [66], which scores the amount of plaque according to the defined criteria (Table 3). The score will be measured full-mouth at each tooth, but only for ‘defined teeth’ (explained above for GI). The ‘Modified plaque index for the patient ‘ is then the mean of the MPIs of the ‘defined teeth’ (Table 2): Index = (Sum of MPI per tooth × 100)/(3 × number of measured teeth). To measure MPI, we will use the following disclosing agent: Mira-2-Ton®, a two-tone erythrosine-free disclosing dye solution (Hager & Werken, Duisburg, Germany), which can help to differentiate blue-dyed elderly plaque from pink-dyed recent plaque. The MPI will be determined clinically by direct assessment of the study participant.

**Table 3 Tab3:** Criteria for the Modified Plaque Index (MPI)

Score	Oral hygiene	Description
0	Very good	No plaque
1	Good	Small plaque areas approximal
2	Moderate	Small plaque areas approximal + cervical
3	Poor	Plaque covers 1/3 of the cervical area of the bracket

### Local cytokine concentration

Sample collection: For the analyses of local inflammation, samples from three different oral niches will be collected longitudinally from baseline until 6 months after insertion of the fixed appliance (T0, T1, T2, T3, T4). Oral niches were selected as one representative of the previously defined three metaniches [52]: 1. Tongue (representing S-T-HP), 2. cheek (representing C-U), 3. gingival crevicular fluid (representing P-GCF) [52]. Study participants will be advised not to eat or drink anything except water up to three hours prior to the study appointment. Therefore, smear soft tissue samples will be collected in Eppendorf tubes from the middle part of the tongue and molar region on the right side of the cheek using sterile swabs wiping over the area several times for about 30 s [52]. Moreover, samples of GCF will be collected from 6 periodontal pockets of the mesio-buccal side of’defined Ramfjord teeth’: 1) in case of fixed appliance in the upper and lower arch ‘defined Ramfjord teeth’ are 16, 21, 24, 36, 41 and 44; 2) in case of fixed appliance in the upper arch only ‘defined Ramfjord teeth’ are 16, 21, 24 and their mirrored partners 26, 11, 14 and 3) in case of fixed appliance in the lower arch only ‘defined Ramfjord teeth’ are 36, 41, 44 and their mirrored partners 46, 31, 34. In case of a missing Ramfjord tooth [63, 64] we will collect GCF from the adjacent and comparable tooth (incisor, premolar, molar). GCF will be gathered using sterile paper strips (Oraflow Inc., New York, USA) in accordance to standardized protocols [21, 22, 52, 67, 68]: usage of cotton rolls for draining, smooth air-drying of the ‘defined Ramfjord teeth’ and careful insertion of paper strips in the gingival sulcus (premolar/molar region 30 s, incisor region 60 s). Sulcus fluid flow rate (SFFR) will be measured using Periotron 8000 (Oraflow Inc., New York, United States) according to the manufacturer’s instructions and will be used to determine the volumes of gingival crevicular fluid according to a calibration curve in order to calculate original cytokine concentrations [52]. Samples will be frozen immediately after collection according to standardized protocols [52].

Evaluation of local cytokine concentration: Tongue and cheek samples will be eluted from swabs by centrifugation and dilution to > 100 µl (Meso Scale Discovery, Rockville, USA, R50AG-2). Elution of proteins samples of GCF collected with six paper strips of one patient will be performed in cold diluent buffer (Meso Scale Discovery, Rockville, USA, R50AG-2). The concentration (in pg/mL) of GM-CSF, IFN-γ, IL-2, IL-4, IL-6, IL-8 and IL-10 as well as TNF will be measured using multiplex immunoassay with a U-PLEX Biomarker Group 1 (hu) assay (Meso Scale Discovery; Rockville, USA, K15067L-2) on a MESO QuickPlex SQ 120 instrument (Meso Scale Discovery; Rockville, USA) in accordance with the manufacturer’s instructions, standardized dilution sequences and in accordance with previous studies [25, 52].

### Oral microbiota

Sample collection: For the investigation of the composition of oral microbiota, samples will be collected in accordance to the sample collection method described above for investigation of local cytokine concentrations using standardized protocols [21, 22, 52, 67, 68] and ‘defined Ramfjord teeth’ are the same as described for local cytokines.

Microbial DNA will be isolated with the ZymoBIOMICS DNA Microprep kit according to manufacturer’s instructions (Zymo Research, Freiburg, Germany). Composition of the oral microbiota will be analysed using 2 × 300 bp paired-end sequencing of the 16S rDNA V1-V3 regions on a MiSeq system (Illumina, San Diego, CA, USA) in accordance with previous studies [52]. Raw reads will be subjected to quality-based filtering and primer sequences will be removed using a combination of Trimmomatic [69] and Cutadapt [70]. Subsequently, we will perform classification to operational taxonomic units (OTUs) and identification of zero-radius OTUs (ZOTU) based on the USEARCH 11 algorithm [71, 72] as implemented in the IMNGS web server [73] and taxonomic classification using the SILVA databases will be used [52, 74]. Further analyses with regard to alpha and beta diversities, correlation and enrichment of OTUs or taxa will be done within R [75] vegan [76] and edgeR [77].

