***Trial registration*:**

This trial is registered at ClinicalTrials.gov in two parts under the number NCT04598633 (Adolescents, registration date 10/22/2020), and NCT04606186 (Adults, registration date 10/28/2020).

T0: Base line; Study time point before the insertion of the fixed appliance.

T1: Study time point ~ 1 week after insertion of the fixed appliance/ start of lozenge intake.

T2: Study time point ~ 4 weeks after insertion of the fixed appliance/ start of lozenge intake.

T3: Study time point ~ 12 weeks after insertion of the fixed appliance/ start of lozenge intake = last day of lozenge intake.

T4: Study time point ~ 24 weeks after insertion of the fixed appliance = 24 weeks after start of lozenge intake = 12 weeks after end of lozenge intake.

T_mem:_ Memory T cells.

T_reg_: Regulatory T cells.

Th_1_: Helper T cells: Th_1_ cells.

Th_2_: Helper T cells: Th_2_ cells.

Th_17_: Helper T cells: Th_17_ cells.

TNF: Tumor-necrosis-factor.

U: Sublingual area.

w: Week(s).

WHO: World Health Organisation.

WRT: Wilcoxon rank-sum test.

WSL: White spot lesions.

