### Explanation for the choice of comparators

In this clinical trial, the influence of *L. reuteri* Prodentis®-lozenges (DSM 17938, ATCC PTA 5289) versus control lozenges on clinical parameters, the oral microbiota and the immune response during an orthodontic treatment in adolescent and adult patients will be compared. The active comparator *L. reuteri* Prodentis®-lozenges (DSM 17938, ATCC PTA 5289; BioGaia AB, Sweden) and the control comparator lozenges (BioGaia AB, Sweden) (Table 1) were chosen since the adjuvant use was proven beneficial concerning oral health [45, 46]. To our best knowledge, the effect of *L. reuteri* Prodentis®-lozenges, which contain two probiotic strains (DSM 17938, ATCC PTA 5289; BioGaia AB, Sweden), has not been studied during orthodontic treatment with fixed appliances so far. Since fixed appliances were shown to lead to strongest side effects shortly after insertion of appliance within the first three months [31, 32], we chose to start lozenge intake from the day of insertion of fixed appliance lasting for 12 weeks. The intake will be two times daily in accordance to the manufacturers’ instructions [60]. Lozenges consist of bulking agent (isomalt), *L. reuteri* DSM 17938 and *L. reuteri* ATCC PTA 5289, fully hydrogenated palm oil, peppermint flavor, menthol flavor, peppermint oil and sweetener (sucralose) [45, 60]. One lozenge consists of a minimum of 200 million live *L. reuteri* Prodentis [45, 60]. They are available under the name *L. reuteri* Prodentis®/™ (BioGaia AB, Sweden) [60]. Control-lozenges will be free of *L. reuteri* strains (Table 1).

**Table 1 Tab1:** List of comparators

Arms	Assigned interventions
Active Comparator: *Limosilactobacillus reuteri* Prodentis®-lozenges (BioGaia)	Dietary Supplement: *Limosilactobacillus reuteri* Prodentis®-lozenges (DSM 17938, ATCC PTA 5289) Two times per day for 12 weeks
Control Comparator: Control-lozenges (BioGaia)	Dietary Supplement: Control-lozenges (BioGaia) Two times per day for 12 weeks

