### Intervention description

Patients will receive lozenges and a protocol, in which they receive information about the intake and storage of lozenges:Supplementary intake of lozenges two times per day (1-0-1) for 12 weeks after the insertion of the fixed appliances (slowly melt on the tongue, mandatory after brushing of teeth)Storage of lozenges at in the refrigerator at 4 °CIntake protocol to control the regular intake of lozengesReturn of canisters for counting of left overs

Further, they receive an intake protocol, in which they should make a note about the daily intake of the lozenges. To control the lozenge intake, patients will be asked to return the used canisters for counting of left overs. Further, referring to adolescent study participants, not only the study participant (adolescent) but also the parent and/or legal guardian will be asked about the maintenance of perfect storage conditions during the study time (lozenge intake). Further, a nutrition protocol will be handed out to all participants to obtain an accurate, self-reported diet history on a daily basis. Participants should list their meals for breakfast, lunch and dinner as well as snacks. Additionally, the average water consumption and drinks containing sugar should be listed. Moreover, a special focus will be on the individual intake of milk products (e.g., yoghurt, cheese, milk), which should be noted in detail. Average consumption of milk products will be allowed.

Study participants in the test and control group will have five study time points (Fig. 2) including a base line check-up and four follow-up consultations during the study period for measurement of clinical parameters and taking of samples (Fig. 2). Sampling and examination according to the time line will be done during routine practice visits. The first consultation will be the base line check-up, where all clinical parameters and samples will be taken. Here, intake and nutrition protocol will be explained to the study participants and lozenges will be handed out to the patient. Day of insertion of fixed appliance is the start of the lozenge intake. There will be four follow-up consultations during the study period, where all clinical parameters and samples will be taken again for longitudinal evaluation. Taking of blood samples ([name]) will only be performed on T0, T2 and T3 and only in the adult group.

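### At T1 to T3 the microbiota comparison cannot separate the presence of the administered L. reuteri from a change in the resident bacteria, most directly on the tongue

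*Protocol article*

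**What the plan says.** All references are to the protocol article.

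- **Product.** Lozenges are taken twice daily for 12 weeks, and the instruction under Intervention description is "slowly melt on the tongue, mandatory after brushing of teeth". Under Explanation for the choice of comparators, "One lozenge consists of a minimum of 200 million live" L. reuteri; the control lozenge has none.
- **Sampling.** Under Local cytokine concentration, swabs are "collected in Eppendorf tubes from the middle part of the tongue and molar region on the right side of the cheek", and crevicular fluid is the third niche. The Oral microbiota section adopts the same collection: "samples will be collected in accordance to the sample collection method described above for investigation of local cytokine concentrations". Samples are taken at T0 to T4.
- **Timing.** The visit definitions after the abstract place T3 at about "12 weeks after insertion of the fixed appliance/ start of lozenge intake = last day of lozenge intake". T1, T2 and T3 therefore all lie within intake; T4 is 12 weeks after it ends.
- **Before the visit.** "Study participants will be advised not to eat or drink anything except water up to three hours prior to the study appointment". The lozenge is not named, and no interval between last lozenge and swab is set or recorded.
- **Assay and analysis.** DNA is extracted and the 16S V1-V3 regions are sequenced. The stated read processing is quality filtering and primer removal. Then "Further analyses with regard to alpha and beta diversities, correlation and enrichment of OTUs or taxa will be done".
- **Question.** The null hypothesis under Objectives includes no difference between arms in the composition of the oral microbiota in a representative of each metaniche. The abstract gives prevention of dysbiosis as part of the aim.

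**The concern.** One arm receives a live bacterium in the mouth and the other does not, and the outcome is an inventory of bacterial DNA in the mouth taken while dosing continues. The test lozenge delivers at least 2 x 200 million = 400 million L. reuteri a day, against none in the control arm. If the processing is followed as written, product reads enter the whole-community comparisons.

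The composition null can then be false because of what was administered, with no change in the bacteria that live there. A T1 to T3 difference could be read as support for the dysbiosis aim when it shows exposure. This matters because the article presents the first three months after insertion as the period of risk and prevention, so the on-intake visits are the ones a reader will look to.

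**Working it through.** **Plan's own figure.** None is given for the microbiota. The primary sample size reproduces: a two-sample t-test with effect size 1, one-sided alpha 0.05 and power 0.85 gives n = 15.10, so 16 per arm (power 0.868), and 34 recruited per age group after 5% drop-out. The check below uses the planned 17 per arm.

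**Step 1: Bray-Curtis.** Let p be the resident profile in both arms and f the share of test-arm reads that is product. The control profile is p; the test profile is (1-f)p plus f on one further taxon. Bray-Curtis = 1 - sum of minima = 1 - (1-f) = f. So f = 1%, 5% and 20% give a dissimilarity of 0.01, 0.05 and 0.20 with no resident change. This is a distance between mean profiles, not a test result, because it ignores variation between participants.

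**Step 2: Simulation.** Assumptions: 17 per arm; identical resident communities (150 taxa, Dirichlet-multinomial with concentration 30 or 100, 10,000 reads); no native L. reuteri; product share log-normal across test-arm participants with mean f, capped at 90%; 200 runs per setting. Tests at 5%: Mann-Whitney on the taxon, t-test on Shannon, PERMANOVA on Bray-Curtis. The article names neither a distance nor these tests, so they are stand-ins. Each range spans the two concentrations.

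| Assumed f | L. reuteri taxon differs | Bray-Curtis rejects | Shannon rejects |
|---|---|---|---|
| 0.1% | 100% | 4-6.5% | 4-5% |
| 1% | 100% | 7-23.5% | 5.5-7% |
| 5% | 100% | 85-99% | 6.5-9% |
| 10% | 100% | 100% | 7-7.5% |
| 20% | 100% | 100% | 28.5-30% |
| 30% | 100% | 100% | 55-65% |

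**Step 3: Direction for Shannon.** H' = (1-f)H + h(f), with h(f) = -f ln f - (1-f) ln(1-f). With an assumed H = 3.5:

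- f = 5%: 3.325 + 0.199 = 3.52
- f = 20%: 2.80 + 0.50 = 3.30
- f = 30%: 2.45 + 0.61 = 3.06

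The index barely moves at small f and falls at large f. The article's Discussion associates lower diversity with periodontal health, so a large product share would look favourable.

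**Step 4: After removal.** With L. reuteri reads removed and the rest re-normalised, rejection across f = 0 to 30% is 1.5-8% for Bray-Curtis and 2-7% for Shannon. With 200 runs, the standard error around 5% is sqrt(0.05 x 0.95 / 200) = 1.5 percentage points, so this is about nominal.

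**The case against.** - **The article is condensed and does not say that product reads will be kept.** True: a reader might infer a decision to count them as a treatment effect, and the text supports no such inference. But the section describes the pipeline down to named tools, and followed as written it leaves them in. The null and the sampling times are fixed here.
- **The no-food rule may be understood to cover a lozenge.** That is a natural reading and would lower f. A reader might infer that participants will routinely take a lozenge just before the swab; the documents do not show this. They leave the point open and record no time.
- **Only one of three niches shares the lozenge's surface.** This stands. Cheek is a different surface, and crevicular fluid is taken from the sulcus after cotton-roll draining and air-drying. Both could be reached only indirectly, to an extent the documents do not quantify.
- **The size is assumed.** This stands. At f = 1% or less, beta diversity is moderately affected at most, and Shannon is close to nominal up to 10%.
- **L. reuteri in a taxon list identifies itself, and its presence is of interest.** Fair: the Discussion cites resistance to colonisation as a mechanism. But a beta-diversity distance does not show which taxon produced it.
- **T4 is off intake.** This stands, and T4 can carry claims of lasting change. It cannot answer what happens to the resident community during intake.

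**Conclusion.** The point holds for T1 to T3, directly for the tongue and only indirectly for cheek and crevicular fluid. At those visits, rejecting the composition null cannot by itself separate product presence from an effect on dysbiosis. Taxon enrichment is affected at any detectable share, beta diversity at an assumed share of about 5% of reads or more, and Shannon only at about 20% or more.

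These thresholds rest on an assumed f and on the simulated community. A reader might infer that the whole microbiota outcome is invalid, or that serious distortion is established. Neither follows: no document gives the read share, two niches are remote from the lozenge, and T4 is not materially affected. The primary gingival index endpoint does not depend on sequencing. This is a correction that should be made to a secondary outcome; it does not threaten the trial's main conclusion.

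**What to change.** In the Oral microbiota section, pre-specify the following:

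1. The T1 to T3 between-arm comparisons of alpha diversity, beta diversity and enrichment are also run after removing ZOTUs assigned to L. reuteri and re-normalising. State the rule by which a ZOTU counts as L. reuteri.
2. Any claim about dysbiosis during intake rests on that resident-community analysis.
3. L. reuteri abundance is reported separately by arm, niche and visit, as a measure of exposure and colonisation.
4. Claims of lasting change rest on T4.
5. The time of the last lozenge before each sample is recorded. The intake schedule is not changed.

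The cost is one filtering step in the R pipeline and one line on the visit sheet; no new samples and no change in sample size. Any native L. reuteri is also removed from the resident-community comparison, but it stays in the separate report. The Trial status section says that no data had been analysed and recruitment was continuing. The filter can therefore still be fixed in advance for everyone, and the lozenge time recorded at the visits that remain.

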### Serum cytokine levels

Sample collection: For the investigation of systemic inflammation, samples of peripheral whole blood (WB) will be taken by puncturing a peripheral (e.g., cubital or cephalic) vein in accordance to standardized protocols [58]: The patient is positioned upright in an adjustable chair followed by application of a tourniquet, selection of a puncture site on the non-dominant arm, site disinfection with a local antiseptic solution (Aseptoderm, [name], Malsfeld, Germany), careful insertion of a butterfly-needle (Safety-Multifly® 21G tube200mm, Sarstedt AG, Nümbrecht, Germany) and taking of blood samples with vacuum syringes with heparine coating(50S-Monovette, Sarstedt AG, Nümbrecht, Germany) [58]. The congestion-to-sample time is kept below 60 s to avoid changes in the blood sample and, after sample collection, the tourniquet and the needle are removed and the puncture site is compressed for 2 min with a sterile compress, followed by adequate dressing [58]. WB samples are taken before insertion of the fixed appliance (T0; baseline), 4 weeks after insertion of fixed appliance and after start of lozenge intake (T2) and 12 weeks after insertion of fixed appliance at the end of lozenge intake (T3) (Fig. 2).

Serum cytokine analyses: Serum will be separated from peripheral whole blood by centrifugation at 2000×*g* for 10 min and stored at -80 °C. Measurement of systemic cytokine concentrations in serum (in pg/mL) will be performed using enzyme-linked immunosorbent assays (ELISA; e.g., Human IL-17 ELISA kit (ab100556), Abcam, Cambridge, UK) or multiplex immunoassay (U-PLEX Biomarker Group 1 (hu) assays from Meso Scale Discovery, Rockville, USA) according to the manufacturer’s instructions and in accordance to previous studies [78–81]. To analyse systemic inflammation and a possible Th_1_ cell (Th_1_) /Th_2_ cell (Th_2_) or Th_17_ shift, pro-inflammatory cytokines and cytokines representing the Th_1_/Th_2_/Th_17_ cytokine profile (e.g. TNF, IFN-γ, IL-10/-17) will be measured [82].

### Frequencies of innate and adaptive immune cells

#### Sample collection

For the investigation of cellular immunity, samples of (heparinized) peripheral whole blood (WB) will be taken by puncturing a peripheral (e.g., cubital or cephalic) vein in accordance with standardized protocols as explained above [58] before insertion of fixed appliance (T0; baseline), 4 weeks after insertion of fixed appliance and after start of lozenge intake (T2) and 12 weeks after insertion of fixed appliance at the end of lozenge intake (T3) (Fig. 2).

Analyses of frequencies of innate and adaptive immune cells: Peripheral blood mononuclear cells (PBMNC) will be separated from whole blood samples by density gradient centrifugation using the Ficoll-Hypaque technique (Biocoll separating solution; Biochrom, Berlin, Germany), washed, suspended in phosphate-buffered saline (PBS; Biochrom, Berlin, Germany) and frozen according to standardized protocols [81, 83–85]. The cellular immune status will be analysed quantitatively and qualitatively (frequencies of immune cells and their subtypes in the PBMNC-fraction) with thawed PBMNC using multiparametric flow cytometry (Cytoflex S, Beckman Coulter, Indianapolis, United States) [81, 83–85]. Lymphocyte typing will be performed using an ‘inflammatory panel’ to quantify different innate and adaptive immune cells, e.g., different CD4 or CD8 T cell subtypes (activated, proliferating/non-naïve/memory (T_pro_, T_non-naïve,_ T_mem_), T helper cells (Th_1_/Th_2_/Th_17_ cells) or regulatory T cells (T_regs_), B cells, natural killer (NK) cells, natural killer T (iNKT) cells and dendritic cells (DC) [81, 83, 84].

